Yoga is an exercise activity that emphasizes controlled, fluid movements through a variety of static postures. Many yoga postures challenge and strengthen musculature of the lower extremity, while minimizing some potential negative effects that other exercise programs pose for people with knee OA. For example, running is an activity that includes large and repetitive loads on the knee, which may not be the best-suited activity for individuals with knee OA. Yoga has beneficial effects on various aspects of quality of life, including improved cardiorespiratory health, body awareness, well-being and mental health. Further, yoga has been shown to improved strength, balance, flexibility, pain, and disability in older adults and individuals with knee OA (12) (13) (14) (15) (16) (17). For example, a pilot study consisting of 7 women over age 50 years with symptomatic knee OA implemented an 8-week program of modified yoga postures. Each week participants attended one 90-minute weekly class. Participants reported improvements in knee pain, physical function and mental health, demonstrating that yoga holds great potential as a treatment option for older, yoga-naive women with knee OA (16).

We recently completed a biomechanical analysis of ten common yoga postures that emphasize lower extremity strengthening, including squats, lunges and balancing postures in 30 young women [not yet published]. These analyses focused on the knee adduction moment and muscle activation patterns to identify postures that did not overload the medial knee while requiring enough muscle activity to result in strengthening. Of the ten yoga postures, eight produced negligible knee adduction moments and all required muscle activations that would facilitate strengthening of the quadriceps and hamstrings [not yet published]. These data provide the foundation for an intervention that emphasizes the eight yoga postures that result in negligible knee adduction moments.

Research Question & Hypotheses

The primary objective of this study is to determine whether a yoga exercise intervention will improve the strength of the musculature that surrounds the knee without increasing knee pain in women with knee osteoarthritis (OA). A secondary objective is to determine whether a yoga exercise intervention will reduce the knee adduction moment during gait, improve mobility performance, and improve cardiovascular fitness.

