Each class will be 1 hour in length. The yoga class will include a warm-up period featuring large body movements with no resistance. Then the instructor will lead the class through a series of standing postures identified with our previous work as requiring high muscle activity from the knee musculature, but minimal knee adduction moment. Examples of these postures include squats, lunges, wide-legged stances in various ranges of knee motion, and balance poses. The instructor will offer a variety of modifications for each pose, to ensure that the participants have an alternative best suited for their experience level. In addition, a series of seated poses that focus on flexibility will be completed. Each class will conclude after a guided deep-breathing and meditation activity. Throughout the class, education about knee joint anatomy, osteoarthritis and proper lower extremity alignment will be included.

Retention strategies to enhance adherence to the exercise intervention will include the following:

- Exercise logbook to track activity,
- $100 stipend upon completion of the final data collection,
- Draw for $5 Tim Horton’s gift certificate at the conclusion of some classes, and
- Rewards for best attendance across 12-weeks including a 3 month yoga pass, yoga mats, water bottles.

Outcome Measures

Outcome measures will be collected at baseline and after completion of the 12-week yoga intervention. These outcome measures will be collected at the MacMobilize Laboratory (Communications Research Laboratory Building, room B110) on McMaster campus. A study limb will be chosen as the most symptomatic knee.

*Primary Outcome Measures*

*A. Strength*

The peak torque developed during knee extension and flexion during a maximum voluntary isometric contraction will be measured by use of a Biodex System 2 isokinetic dynamometer. Data will be presented as Nm/kg. After a submaximal practice, 5 maximum-effort trials of isometric knee extension, with the knee joint positioned at 65°, will be recorded. The same protocol will be repeated for isometric knee flexion. The peak value for each of knee extension and flexion will be extracted. The reliability for these data are excellent (r=0.96) (26).

*B. Pain*

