- The Knee Osteoarthritis Outcome Score (KOOS) is a patient-administered, 42 item questionnaire.  Study participants are asked to answer questions on a 5-point Likert scale, which takes approximately 10 minutes to complete.  The KOOS consists of 5 subscales:  pain, other symptoms, activities of daily living (ADL), function in sport and recreation and knee-related quality of life (QOL).  The questionnaire results in a normalized score out of 100 for each subscale, where 100 indicates no symptoms and 0 indicates extreme symptoms. The questionnaire relies on subject’s recall from the previous week.

The KOOS has been used in persons 13-79 years of age. The KOOS reference values are available from various sample populations including; age/sex based samples (33) (34), active soccer players (35), and male and female patients post anterior cruciate ligament reconstruction (36). The KOOS has a high test-retest reliability demonstrated by intra-class correlation coefficients of 0.80-0.97 for the Pain subscale, 0.74-0.94 for the Symptom subscale, 0.84-0.94 for the ADL subscale, 0.65-0.92 for the Sport/Rec subscale and 0.60-0.91 for the QOL subscale in patients with knee osteoarthritis (OA) (37). The minimal detectable change values for patients with knee OA are 13.4 for Pain, 15.5 for Symptoms, 15.4 for ADL, 19.6 for Sport/Rec, and 21.1 for QOL (38). Currently, the minimal clinically important change value is suggested to be 8-10 for the KOOS, proving the scale is sensitive to change (38). The KOOS has been reported to detect change following surgical procedures including; ACL reconstruction, meniscectomy, cartilage repair procedures, tibial osteotomy, total knee replacement and non-surgical procedures including; physical therapy, as well as nutritional and pharmaceutical interventions (39). The KOOS presents an internal consistency range (Cronbach’s α) of 0.65–0.94 for Pain, 0.56–0.83 for Symptoms, 0.78–0.97 for ADL, 0.84–0.98 for Sport/Rec and 0.71–0.85 for QOL in patients with knee OA (38). The KOOS has demonstrated convergent and divergent construct validity when compared against numerous instruments including the different subscales of the Short Form-36 and the Lysholm knee scoring scale (38).

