The KOOS includes the complete and original WOMAC OA Index LK 3.0 therefore WOMAC scores can be calculated in isolation. The KOOS subscales ‘Sport and Recreation function’ and ‘Quality of Life’ have been shown to be more sensitive and distinct than the WOMAC subscales ‘Pain’, ‘Stiffness’, and ‘Function’ when studied in subjects with radiographic evidence of OA who underwent a meniscectomy 21 years prior to the study (mean age = 57 years, range = 38-76) compared to age and gender matched controls (40).

*Secondary Outcome Measures*

*A. Biomechanical Analyses of Gait and 3 Yoga Postures*

Participants will change into shorts, a sports bra, and be barefoot. The participants’ height, body mass, lower limb length, anterior superior iliac spine (ASIS) distance, posterior superior iliac spine (PSIS) distance, upper thigh circumference, abdominal circumference knee width, calf circumference and ankle width will be measured. Then, 3 rigid body marker clusters will be placed on the participant with Velcro straps. These will be placed between the left and right PSIS, on the study thigh, shank and the top of the foot. These correspond to the specifications required to create a lower-body model. Landmarks will be digitized in reference to the rigid body marker clusters. These landmarks include: both left and right ASIS, iliac crest, PSIS, greater trochanter, lateral and medial distal femoral condyles, lateral and medial tibial proximal condyles, lateral and medial malleoli, tibial tuberosity, proximal fibular head, head of metatarsals 1, 2, 5, and calcaneus.

With the participants on a force plate and in the field of view of three banks of Optotrak cameras (which record only positions of the markers), a 5 second standing reference trial will be collected for the motion capture system. Participants will be instructed to perform 10 hip rotations, 5 in each direction. Participants will be instructed to perform 5 knee flexions and extensions of both legs. Participants will be asked to perform 3 yoga postures (squat, lunge and wide-legged stance) for 10 seconds with at least a 10 second rest in between each posture. The order of these postures will be randomized between participants. Finally, participants will be asked to walk across the 10 foot motion capture area. For each yoga posture and gait, 3 successful trials will be recorded.

*B. Mobility Performance Measures*

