*Baseline Measures: MacMobilize Laboratory at McMaster University, Hamilton*

1. Written, informed consent
2. Anthropometric Measurements
3. Resting Heart Rate and Blood Pressure
4. Instrumentation & Biomechanical Analyses (Gait and Yoga)
5. Mobility Performance Measures
6. Strength Assessment
7. Questionnaire: KOOS
8. YMCA protocol

This laboratory visit will require 2.5 hours to complete.

*Yoga Intervention: De La Sol Yoga at [name], Hamilton*

- 12-week intervention
- Requesting attendance to 3 supervised classes each week

Each yoga class will be 1 hour.

*Follow-up Measures*

1. Anthropometric Measurements
2. Resting Heart Rate and Blood Pressure
3. Instrumentation & Biomechanical Analyses (Gait and Yoga)
4. Mobility Performance Measures
5. Strength Assessment
6. Questionnaire: KOOS
7. YMCA protocol
8. Stipend

This laboratory visit will require 2.5 hours to complete.

Sample Size Estimation

Systematic reviews of the effectiveness of resistance training for improving self-reported physical function and isometric knee strength in knee OA had average effect sizes of 2.11 and 0.41 respectively (5). Given the lower effect size (0.41) and a Type I error = 0.05 on a 1-tailed test (based on strong evidence of improvement), a sample of 39 participants is necessary to yield 80% power to detect a significant effect. We aim to recruit 45 participants to account for drop-outs and losses to follow-up.

Statistical Analyses

Descriptive statistics will be determined for all of the outcome measures. Repeated measures analysis of variance will be used to determine if changes in the primary and secondary outcome measures as a result of the yoga exercise intervention. The p value will be set at p<0.05.

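### The KOOS, which carries the primary pain outcome, is completed after knee-loading tests at both visits, so same-day pain may colour it, possibly unequally before and after training

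*Protocol*

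**What the plan says.** The primary objective in the Protocol's Introduction is to "improve the strength of the musculature that surrounds the knee without increasing knee pain", so pain stands beside strength as a primary outcome. Under Primary Outcome Measures, B. Pain, one instrument is described: "The Knee Osteoarthritis Outcome Score (KOOS) is a patient-administered, 42 item questionnaire". The same section adds: "The questionnaire relies on subject’s recall from the previous week".

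The order of testing is set out in the numbered Baseline Measures and Follow-up Measures lists. They begin with consent (baseline) or anthropometry (follow-up) and end with the cycle test or the stipend, so they read as chronological. The baseline list has "7. Questionnaire: KOOS"; at follow-up the KOOS is item 6, because there is no consent item. At both visits the following come first:

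- **Biomechanics:** gait trials and the postures. "Participants will be asked to perform 3 yoga postures (squat, lunge and wide-legged stance) for 10 seconds", with three successful trials recorded for each posture.
- **Mobility:** the six-minute walk, a 9-step staircase climbed and descended at the best safe speed and done twice, and the 30-second chair stand.
- **Strength:** "5 maximum-effort trials of isometric knee extension", then the same protocol for flexion.

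Of the tests, only the YMCA cycle test comes after the KOOS. The protocol states no rest before the questionnaire and no instruction to set aside pain felt during testing.

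**The concern.** A woman with knee osteoarthritis answers questions about the past week's knee pain just after a series of tests that load that knee. Current pain can colour recall, and she may count the test day as part of the week. The protocol itself gives reason to take this seriously: its Introduction links repeated loading to more intense knee pain in this disease.

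The study compares one group before and after yoga. If the test battery affected KOOS answers by different amounts at the two visits, the difference would go straight into the estimated change in pain. If the effect were smaller at follow-up, it could look like benefit or mask a real rise in pain. If it were larger, it could hide a benefit or look like harm. Either way it would bear on whether strength improved without more pain. No analysis could recover the unprovoked scores afterwards.

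**Working it through.** **1. The plan's own figure.** Sample Size Estimation gives 39 participants for an effect size of 0.41, one-tailed 5% error and 80% power. A paired t-test with the noncentral t distribution reproduces this: n = 39 gives power 0.808 and n = 38 gives 0.798. The order of testing does not change this figure. I use n = 39 below.

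**2. When carry-over cancels.** Let T0 and T1 be the true mean KOOS Pain scores for the past week at baseline and follow-up (higher is better). Let c0 and c1 be the mean points lost because the questionnaire follows the tests. Then

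observed mean change = (T1 − c1) − (T0 − c0) = (T1 − T0) + (c0 − c1).

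The bias is b = c0 − c1. If c0 = c1, then b = 0 and the mean change is unaffected. If c0 > c1 the bias favours yoga, and if c0 < c1 it runs against it.

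**3. Can the sign of b be read from the documents?** Two considerations pull in opposite directions.

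- The Yoga Intervention section lists squats, lunges and wide-legged stances among the class postures, and these are the three postures tested in the laboratory. After 12 weeks of practice they may provoke less pain.
- Much of the battery is not a fixed load. Torque is a maximal effort, the stairs are done at the best safe speed, and the walk and chair stands are self-paced. Stronger women may push harder, climb faster and walk further, and so load the knee more at follow-up.

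The sign is therefore unknown, and no section gives a size.

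**4. Illustration of what a small difference would do.** Assumptions, none of them from the protocol: no true change, an SD of individual KOOS Pain change of 10 to 20 points, and a difference |b| of 0, 2 or 4 points. The planned repeated measures ANOVA with two time points is equivalent to a two-sided paired t-test. With n = 39 there are 38 degrees of freedom, and the noncentrality is (|b| / SD) × √39, with √39 = 6.245. For |b| = 2:

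- SD 10: 0.200 × 6.245 = 1.249
- SD 15: 0.133 × 6.245 = 0.833
- SD 20: 0.100 × 6.245 = 0.625

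Probability of p < 0.05 when pain has not truly changed:

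| Difference in carry-over, either direction | SD 10 | SD 15 | SD 20 |
|---|---|---|---|
| 0 points | 0.050 | 0.050 | 0.050 |
| 2 points | 0.230 | 0.128 | 0.093 |
| 4 points | 0.682 | 0.368 | 0.230 |

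The two-sided rates are the same for either sign of b; only the direction of the false result differs.

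**5. Scale.** Primary Outcome Measures, B. Pain, gives an important change of 8 to 10 points. Two points is 2/10 = 20% to 2/8 = 25% of that, so a difference well below clinical importance could still affect the test.

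**The case against.** The strongest reply is that nothing in the protocol shows a bias. The KOOS asks about a week, not the moment. The order is identical at both visits, so a constant carry-over drops out. The tests are also fairly mild: postures are held for 10 seconds with at least 10 seconds of rest, women may stop during the walk, the handrail is allowed on the stairs, and women with patellofemoral symptoms or unable to climb two flights safely are excluded. All of this stands, and it makes the point a risk rather than a demonstrated error.

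A reader might go further and infer that the women are untrained at baseline, so that the flare must shrink by follow-up and the bias must favour yoga. The documents do not support that. The exclusion criteria do not mention yoga or exercise experience, recruitment uses posters and newsletters from the yoga studio itself, and the classes offer modifications for different levels of experience. As shown above, the tests could load the knee more at follow-up.

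A last objection is that moving the questionnaire is not quite free. The KOOS takes about 10 minutes and is the only listed seated item between maximal strength testing and the YMCA test, which predicts VO2max from heart rate. That is correct, and the fix allows for it.

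What the reply does not remove is that cancellation needs equal carry-over at both visits, which the design neither ensures nor can check.

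**Conclusion.** The point holds as an avoidable risk of bias in a primary outcome. The order of testing, the role of the KOOS and the absence of a control group are all in the protocol. That same-day pain influences one-week recall is plausible but not shown. That it does so unequally at the two visits is possible, with unknown direction and size.

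It would be wrong to say that the pain outcome is contaminated, or that the bias flatters yoga. The range of about 9% to 23% for a 2-point difference rests on assumed inputs (n = 39, SD of change 10 to 20, no true change) and shows sensitivity only. With no difference the error rate is 5%. The stated sample size is unaffected. The change is worth making because it costs little and the problem cannot be repaired once data are collected.

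**What to change.** In both visit lists, move the KOOS ahead of all physical testing: directly after written consent at baseline, and as the first item at follow-up. Leave the order of the remaining tests as it is.

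Because the questionnaire would no longer separate strength testing from the YMCA test, insert a brief seated rest there, of the same length at both visits, so that the heart-rate-based estimate is taken under like conditions.

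The cost is an edit to two lists and possibly a few minutes added to the 2.5-hour visit. No test, staff or sample-size change is needed.

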**A Yoga Exercise Intervention Designed for Women with Knee Osteoarthritis**

**Protocol**

**Introduction**

Over 4 million Canadians endure a form of arthritis (1). This number will escalate because, as a nation, we are getting older and heavier at an alarming rate (1). Arthritis is the single greatest cause of chronic disability among community-dwelling older adults, by painfully restricting mobility in daily life (2). The most common arthritis, osteoarthritis (OA), affects 10% of Canadian adults (1). Osteoarthritis results from excessive and abnormal loads that degrade cartilage and bone, most frequently in the knee. Adding to the complexity of treatment, knee OA rarely occurs in isolation. This population has elevated incidences of cardiovascular and gastrointestinal disorders and depression (1).

Keeping older adults with knee OA moving is critically important but not straight-forward. Systematic reviews and clinical practice guidelines confirm that exercise is critical in knee OA treatment (3-5). Exercise reduces symptoms, co-morbidity and improves physical function (3-5). In fact, the effects of aerobic and strengthening exercise on pain are equivalent to medication (5). However, important caveats exist. Generic exercise prescription in large samples produces mediocre findings in terms of pain and physical function (3). It is important to note that these exercise programs did not benefit from data that would properly dose the type, intensity, repetition and biomechanical load of the exercise for people with knee OA.

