**Study Design and Methods**

This intervention study features a repeated measures design. Outcome measures will be assessed at McMaster University before and after a 12 week intervention. The yoga exercise intervention will be delivered at a yoga studio in downtown Hamilton, Ontario. This proof of principle study will aim to provide preliminary data supporting the use of a yoga exercise intervention in a sample of women with knee OA.

Participants

Fifty community-dwelling women, 50 years of age and older, who meet the American College of Rheumatology (ACR) criteria for clinical knee OA will be recruited to participate in this study. The ACR clinical criteria require 3 of the following:

- Knee pain on most days of the week,
- Less than 30 minutes of morning stiffness,
- Crepitus with active range of motion,
- Bony enlargement,
- Bony tenderness to palpation, and
- Signs of inflammation (warmth, swelling).

*Inclusion and Exclusion Criteria*

Women were selected because incidence of knee OA is two times greater among women than men over the age of 50 years (18-20). Muscle weakness is of particular concern in women with knee OA because their absolute muscle strength is lower compared to men, and therefore women are closer to the critical thresholds of strength required for activities of daily living (21). Finally, women report pain secondary to knee OA more frequently than men (20) perhaps because the pain experience is different (22). The incidence and prevalence of knee OA increases with age, particularly in women (18, 20, 23-25).

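### The sample size is computed for a one-tailed 0.05 test, but the planned repeated measures ANOVA at p<0.05 has no one-tailed provision; read as written, 39 completers give about 70% power, not 80%

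*Protocol*

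**What the plan says.** Sample Size Estimation takes the smaller of two effect sizes from systematic reviews of resistance training, 0.41 for isometric knee strength, and states the basis of the calculation: "Given the lower effect size (0.41) and a Type I error = 0.05 on a 1-tailed test (based on strong evidence of improvement"). It concludes that "a sample of 39 participants is necessary to yield 80% power to detect a significant effect", and plans to recruit 45 to allow for losses.

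Statistical Analyses, directly below, states that "Repeated measures analysis of variance will be used to determine if changes in the primary and secondary outcome measures" have occurred, and adds: "The p value will be set at p<0.05". It mentions no tail, no halving of the p value and no check of direction.

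Study Design and Methods describes a repeated measures design with no comparison group and fixes two measurement occasions: "Outcome measures will be assessed at McMaster University before and after a 12 week intervention".

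**The concern.** The sample size and the analysis appear to describe different tests. A one-tailed paired test at 0.05 puts the whole 5% in the favourable direction. A repeated measures ANOVA with two time points tests the squared t statistic, so its 5% is shared between improvement and deterioration, and it needs a larger observed change to reach significance.

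Two things are at stake. The protocol's only power statement may not apply to the analysis it specifies. The decision rule is also left unclear for a band of results: with 39 completers, a favourable t between about 1.69 and 2.02 is significant under the one-tailed rule and not significant under the ANOVA at face value.

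**Working it through.** **Inputs from the protocol**
- Effect size 0.41, alpha 0.05 one-tailed, power 80%, n = 39, recruitment 45 (Sample Size Estimation).
- Repeated measures ANOVA, p<0.05 (Statistical Analyses).
- One group, two assessments (Study Design and Methods).
- Fifty women as the other recruitment figure (Participants).

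**Assumption.** 0.41 is the mean paired change divided by the SD of the change (d_z). The protocol does not state the scaling; step 1 shows that its 39 implies it.

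**Step 1: reproduce the 39.** For a paired t-test, df = n − 1 and the noncentrality is d_z × √n. One-tailed power is P(T > t(0.95; n − 1)), with T noncentral t.
- n = 38: noncentrality 0.41 × √38 = 2.527, power 79.8%.
- n = 39: noncentrality 0.41 × √39 = 2.560, critical t = 1.686, power 80.8%.

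The smallest n reaching 80% is 39, exactly as stated. The normal approximation, ((1.645 + 0.842)/0.41)² = 36.8, rounds up to 37, which is close. A two-sample calculation would need 74 per arm one-sided, so that is not what was done.

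**Step 2: identify the planned test.** With two time points the time effect has 1 and n − 1 degrees of freedom, and F = t². Rejecting when F exceeds its 95th percentile on 1 and 38 df (4.098) is the same as rejecting when |t| > √4.098 = 2.024. That is the two-sided 0.05 paired t-test.

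**Step 3: power of the planned test at d_z = 0.41**

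| Completers | Power, two-sided 0.05 |
|---|---|
| 39 | 70.4% |
| 45 (no losses) | 76.7% |
| 48 | 79.5% |
| 49 | 80.3% |
| 50 (no losses) | 81.1% |

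The noncentral F calculation with noncentrality n × d_z² (39 × 0.41² = 6.56) gives the same 70.4% for n = 39.

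**Step 4: detectable change.** With 39 completers, two-sided power reaches 80% at d_z = 0.46.

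**Step 5: sensitivity to the scaling of 0.41.** If 0.41 were instead scaled by the between-subject SD, then d_z = 0.41/√(2(1 − ρ)), where ρ is the pre-post correlation. The protocol gives no ρ; the values below are assumptions.

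| Assumed ρ | d_z | One-tailed power, n = 39 | Two-sided power, n = 39 |
|---|---|---|---|
| 0.3 | 0.347 | 68% | 56% |
| 0.5 | 0.410 | 81% | 70% |
| 0.7 | 0.529 | 95% | 90% |

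The absolute level moves a good deal with ρ, but in each row the two-sided power is below the one-tailed power.

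**The case against.** The strongest reply is that the protocol does state its sidedness in advance: "on a 1-tailed test (based on strong evidence of improvement"). The study hypotheses are directional, p<0.05 is compatible with a one-tailed level, and nowhere does the protocol call the test two-sided. With two time points a one-tailed criterion can be carried out by checking the direction and halving the ANOVA p value, and that detail could sit in an analysis plan that is not shown. Part of this stands. The two-sided character follows from the named test and is not stated. It does not remove the inconsistency, because the tail appears only in the sizing sentence, while the analysis section fixes an F test and a threshold that, taken as written, reject in both directions.

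The reply also disposes of a stronger reading. A reader might infer that interpreting the F test one-sidedly would be a post hoc change of error rate. The documents do not support that, since the one-tailed level was declared before data collection.

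A reader might also infer that the Introduction undercuts the case for one tail, since it says "Generic exercise prescription in large samples produces mediocre findings in terms of pain and physical function (3"). That remark concerns pain and physical function under generic exercise; the power calculation concerns knee strength after resistance training. It is not evidence against the one-tailed choice for strength.

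Finally, this is a single-group proof of principle study, and an F test at face value is stricter than the declared one-tailed level, so false positives are not inflated. That is correct and bears on severity. The protocol nevertheless makes a formal power claim, and the claim should match its test.

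**Conclusion.** The point holds as an inconsistency between two adjacent sections; it is not an arithmetic error. The 39 is exact on its own inputs. Under the repeated measures ANOVA as written, 39 completers give about 70% power at a standardised change of 0.41, so the risk of missing that change is about 30% and not the planned 20%. Full completion by all 45 recruits would still leave power just under 77%.

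These figures rest on two conditions: that the ANOVA is applied at an unhalved 0.05, and that 0.41 is scaled by the SD of the change. A reader might take 70% as the study's true power. The documents do not support that, because they give neither the scaling of the cited effect size nor a pre-post correlation. What is supported is a loss of about 10 percentage points on the protocol's own inputs. Severity: should-fix.

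**What to change.** Make Sample Size Estimation and Statistical Analyses describe the same test before any data are seen. Either option is coherent:

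1. Keep the ANOVA as a two-sided test and restate the sizing sentence: 39 completers give about 70% power for a standardised change of 0.41 and 80% power for 0.46, at two-sided 5%.
2. Keep the one-tailed choice and specify in Statistical Analyses a one-sided paired t-test at 0.05 for strength, reported with a two-sided 95% confidence interval. The stated 80% with 39 completers then stands.

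In both cases, say that 0.41 is taken as the mean change divided by the SD of the change.

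The cost is one or two sentences and no additional participants. Option 1 makes the quoted power less favourable; option 2 commits the strength analysis to one direction.
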